#### Data collection

Participants will give consent and complete case report forms (CRFs), including demographic information and questionnaires, via a secure REDcap weblink which will save data directly to UCL's data safe haven. In the event that participants are not able to complete the electronic consent and CRF, they will be able to attend clinic to complete a paper-based consent form and CRF. Cognitive assessment 1 and 2 will be completed in clinic, and cognitive assessment 3 will be completed remotely.

#### Data analysis

Within the cross-sectional dataset investigation of the relationships between cognitive function, fatigue, sleep disturbance, anxiety/depression and social isolation will be undertaken using linear mixed models accounting for demographic factors.

#### 5.2.1.1 MRI substudy

We will scan the brains of 100 participants on a Siemens 3T Prisma scanner at the Clinical Imaging Sciences Centre, University of Sussex. Of the 100 participants scanned, 60-70 will be long Covid patients recruited primarily from the Sussex memory clinic as part of Workstream 1. The remaining participants will be age and sex matched healthy controls (n=30-40). The scan protocol will include the following sequences:

- T1-weighted (whole brain and regional volumes)
- FLAIR (white matter hyperintensity volume, a measure of vascular damage)
- Diffusion tensor imaging (structural connectivity)
- NODDI (microstructural integrity)
- Resting state fMRI (functional connectivity)
- ASL (cerebral blood flow and blood brain barrier permeability)

- Quantitative Susceptibility Mapping (molecular composition and cellular architecture of the tissue)

The aim of this MRI substudy is to determine the neuroimaging correlates of cognitive impairment in long Covid.

#### MRI data collection

Cognitive testing and MRI scanning will take place once, at study entry, noting also the interval between the date of acute infection and test date.

#### MRI data analysis

MRI analyses will be undertaken using the freely available, open-source tools. These tools include NiftySeg (<https://github.com/KCL-BMEIS/NiftySeg>), NiftyFit (<https://discovery.ucl.ac.uk/id/eprint/1489639/>), Matlab's NODDI toolbox (<http://mig.cs.ucl.ac.uk/index.php?n=Tutorial.NODDI matlab>), ExploreASL (<https://sites.google.com/view/exploreasl>) and Freesurfer (<https://surfer.nmr.mgh.harvard.edu>). Using these software packages, we will be able to assess the impact of cognitive Covid on various measures of brain health, such as whole brain and regional volumes, microstructural integrity, structural and functional connectivity and cerebral blood flow.

#### 5.2.2 Work Stream 2: Use of neuropsychological rehabilitation to aid recovery from cognitive Covid

The second workstream will develop a suite of phenotype-specific and evidence-based neuropsychological rehabilitation packages targeted at the cognitive domains primarily affected in cognitive Covid, using functional and quality of life outcomes to measure treatment efficacy. This collection of strategies will be informed by outcomes from workstream 1 and co-produced in collaboration with a group of people living with cognitive Covid-19 (we will refer to this group as Experts by Experience).

#### Intervention Development.

We will develop phenotype-specific neuropsychological rehabilitation plans targeting the predominantly affected cognitive domains as uncovered in Workstream 1, with methods informed by past work on use of neuropsychological rehabilitation to alleviate cognitive deficits arising from CNS infection. To allow for anticipated heterogeneity in the severity and range of cognitive impairment in people with long Covid, different types of cognitive intervention will be employed, including remediation techniques (e.g. improving attention by lengthening the time to complete simple tasks), compensatory and adaptive strategies (e.g. use of memory notebooks and mnemonics). Our neuropsychological rehabilitation plans for Covid-19 will follow the 2013 NICE guidelines on Stroke rehabilitation (section 1.4. Cognitive functioning), 2013 SIGN guidelines on Brain Injury Rehabilitation and evidence

provided by recent systematic reviews SIGN advises on the approach to address the rehabilitation of memory, attention and executive function and recommends the use of therapies such as meta-cognitive strategies (e.g. problem-solving, goal-management and strategic reasoning to treat executive dysfunction, task-specific training for attentional deficits and the use of external aids (e.g. digital diaries) and internal strategies (e.g. use of visual imagery) for mild-moderate memory problems. Likewise, the NICE guidelines recommend that attention training is focused on relevant functional tasks and training on the use of internal strategies to encode information to treat memory problems, as well as environmental strategies (e.g. environmental prompts) and use of external aids. The goal of the intervention trialled in WS2 is to reduce disability due to 'cognitive Covid' and restore a level of function as similar as possible to level pre-infection.

The interventions will be delivered in 10 individual sessions of 1 hour duration over a period of 3 months (1 session per week approximately). In the first session relevant goals will be identified, alongside with a suite of strategies adjusted to the individual needs based on: 1) existing strategies already tried by the individual and found successful, 2) information from WS1 about the individual's profile of cognitive impairment (e.g. dominant dysexecutive function vs dominant amnesic impairment) and 3) personal preferences.

Each therapy session will include, among others: training on restorative strategies to support the learning of new information., modelling of specific strategies and skills, improving the efficiency of existing strategies and improvement or compensation of attentional and concentration disorders. Some of the strategies that will be implemented: goal management training, chunking, pacing, environmental modifications, dual-task training and multimodal encoding. Participants will receive tasks to complete in between sessions and apply in everyday situations. Strategies will be refined and adjusted over sessions as needed.

At the end of the data collection, participants in the control group will be invited to an online workshop where they will receive information about the study findings and about how to use for their benefit the rehabilitation strategies and techniques found successful in the intervention group. Anonymised feedback collected from their participation in these meetings will inform our creation of educational material and tutorials that will be eventually made freely available on NHS websites.

Following work completion, we will produce a Covid-19 Cognitive Recovery Guide (CICERO-Rehab). This is a manual for future clinical usage, describing a step-by-step approach to the rehabilitation to this patient group as developed in the study. The guide will include the approach for adapting the cognitive rehabilitation intervention to different cognitive Covid-19 phenotypes.

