### 7.1 Power calculation

Evidence from the GREAT trial of cognitive rehabilitation in neurodegenerative disease using the same primary outcome Bangor Goal Setting Interview (BGSi) indicated an effect of approximately 0.8 in a population with dementia. This is likely to be an underestimation of the effect in this study as it is likely that the intervention will be more effective in people without neurodegeneration as seen in the population in the GREAT trial.

Assuming a minimally clinically important difference of 2 points (<https://www.thecopm.ca/faq/>) and a more conservative effect of 0.7 would require SD of the measure to be approximately 2.86. Baseline SD observed in the GREAT trial was 1.74, it is likely that variability in our sample is likely to be larger and therefore we can accommodate an Increase in variability of approximately 65%.

A sample of 88 (44:44) will be required to detect an effect of 0.7 on the BGSi at 3 months with 90% power at a 5% significance level. Incorporating an attrition of 25% will require recruitment and randomisation of 118 participants (59:59).

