### **4.1 SAMPLE SIZE JUSTIFICATION**

A sample of 88 (44:44) will be required to detect an effect of 0.7 on the BGSI at 3 months with 90% power at a 5% significance level. Incorporating an attrition of 25% will require recruitment and randomisation of 118 participants (59:59). Therefore, 120 participants will be recruited from the same clinics. Participants in WS1 can if desired take part in WS2.

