### **4.2 RANDOMISATION**

Randomisation will take place once consent and baseline data collection has been completed. Randomisation will be on a 1:1 allocation (intervention:control) via a secure online system hosted by NWOORTH, Bangor University. The system will employ a dynamic adaptive randomisation algorithm. The randomisation will be stratified for centre (London/Sussex/Southampton/Manchester). A member of the research team at UCL will enter the participants details into the web form and perform the randomisation, which will either display directly on screen, if the researcher is unblinded or notification of the randomisation result will be sent to the designated parties to organise ongoing contact.

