### **4.3 LEVELS OF CONFIDENCE AND P-VALUES**

All statistical tests will be two-sided and performed using 5% level of significance. All confidence intervals presented will be 95%, unless stated otherwise.

Secondary outcomes will not be adjusted for multiple comparisons, as standard. The primary outcome is powered for at the significance level stated. Analysis of all secondary outcomes is considered exploratory, and any statements of results related to these outcomes will be reported appropriately.

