## 6.6 ANALYSIS OF PRIMARY OUTCOME

The primary outcome, the BGSi (attainment score) at the 3 months, will be analysed using a multi-level (mixed effect) linear regression model to assess the differences between the two treatment arms. Stratification variables (Site) will be incorporated into the model as a random effect along with gender, age (continuous), years of education (continuous) and RBANS composite score at baseline as fixed factors. Baseline BGSi attainment score will also be incorporated to account for any differences at baseline.

The BGSi at 6 months will be analysed as a secondary outcome using the same model structure as the primary. Unadjusted (section 6.5) and adjusted results will be presented with associated 95% confidence intervals.

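### If intervention participants share therapists, the primary model leaves out a source of variation present in one arm only, so its confidence interval may be too narrow

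*Combined protocol and SAP*

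**What the plan says.** - **Delivery.** Protocol 5.2.2 (Intervention Development): "The interventions will be delivered in 10 individual sessions of 1 hour duration", spread over 3 months, with goals and strategies fitted to the individual.
- **Control.** Protocol 5.2.2.1 and SAP 3.3 describe an individually randomised comparison with standard of care. Controls therefore have no study therapist.
- **Sample size.** Protocol 7.1 (Power calculation): "A sample of 88 (44:44) will be required to detect an effect of 0.7" on the Bangor Goal Setting Interview (BGSI) at 3 months. SAP 4.1 repeats this, "with 90% power at a 5% significance level". Allowing for 25% attrition gives 118 randomised (59:59). No ICC, design effect, caseload or number of therapists is given.
- **Primary model.** SAP 6.6: "Stratification variables (Site) will be incorporated into the model as a random effect". The fixed terms are gender, age, years of education, baseline RBANS composite and baseline BGSI attainment.
- **Other analyses.** SAP 6.9 covers multiple imputation against complete cases, number of sessions, treatment windows and timing of follow-up. SAP 6.10 covers BGSI readiness, importance and difficulty. Therapist appears in neither.

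**The concern.** When one therapist treats several participants, part of each outcome may depend on that therapist. Participants of the same therapist then carry less information than the same number of independent people. Here this can happen in the intervention arm only, which makes the design partially nested.

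A site random intercept does not deal with it. It moves both arms of a site by the same amount and largely cancels from the treatment comparison. A therapist effect moves treated participants only and stays in the comparison. The session-count and treatment-window analyses in 6.9 concern dose and timing, not correlation between participants of one therapist.

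At stake is the width of the primary confidence interval and the true error rate of a nominal 5% test. If a few therapists do much better or worse than others, the plan also has no analysis that would show it. That matters because the protocol intends to produce a rehabilitation manual for wider clinical use.

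**Working it through.** **Inputs from the documents.** Effect 0.7 SD and 44 analysed per arm (protocol 7.1, SAP 4.1); 90% power at 5% (SAP 4.1); two-sided tests (SAP 4.3: "All statistical tests will be two-sided and performed using 5% level of significance"); 1:1 allocation (SAP 4.2); attrition 25%.

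**Inputs assumed.** Number of therapists k = 3 to 9, equal caloads m = 44/k, each participant with one therapist, and ICC 0.01 to 0.10.

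**1. The plan's own figure.** A two-sided two-sample t-test on independent observations at 0.7 SD needs 43.87 per arm, so 44. Power at 44:44 is 90.1% (90.7% by normal approximation). Then 88/0.75 = 117.3, which rounds up to 118. The stated numbers reproduce exactly with no clustering term.

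**2. Effect on the standard error.** With therapist variance in the intervention arm only:

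- Design effect in that arm: DE = 1 + (m − 1) × ICC
- True variance of the difference: SD² × (DE + 1)/44, against SD² × 2/44 if therapist is ignored
- Ratio of true to model standard error: R = √((DE + 1)/2)
- Type I error of the analysis without therapist: 2 × [1 − Φ(1.96/R)]

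Worked case, k = 4 and ICC 0.05: m = 11; DE = 1 + 10 × 0.05 = 1.50; R = √(2.50/2) = 1.118; 1.96/1.118 = 1.753; type I error about 8.0%.

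| Therapists (assumed) | ICC 0.01 | ICC 0.02 | ICC 0.05 | ICC 0.10 |
|---|---|---|---|---|
| 3 | 5.8% | 6.6% | 9.1% | 13.1% |
| 4 | 5.6% | 6.2% | 8.0% | 11.0% |
| 6 | 5.4% | 5.7% | 6.9% | 8.8% |
| 9 | 5.2% | 5.4% | 6.1% | 7.3% |

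**3. Does the site random effect absorb it?** A simulation fitted a site-random-intercept model without therapist or covariates (maximum likelihood, z test, 44:44, assumed site ICC 0.02, 1,500 runs per case, Monte Carlo error about 0.6 to 0.8 points).

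| Setting | ICC 0 | ICC 0.05 | ICC 0.10 |
|---|---|---|---|
| 4 therapists, one per site | 5.3% | 8.9% | 12.1% |
| 6 therapists in 3 sites | 4.5% | 8.0% | 11.0% |

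The inflation remains with site in the model.

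**4. Power.** The normal approximation is Φ(0.7/√((DE + 1)/44) − 1.96).

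- k = 4, ICC 0.05: 0.7/√(2.50/44) = 2.937, giving 83.6%.
- With Satterthwaite degrees of freedom, (1.5 + 1)²/(1.5²/3 + 1²/43) = 8.1, the same case gives about 73%. The two methods differ by about 10 points when therapists are few.
- k = 9, ICC 0.01: 90.2% by normal approximation.

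**5. Baseline adjustment works the other way.** The sample size takes no credit for it. With an assumed correlation of 0.5 between baseline and 3-month BGSI, residual variance falls by the factor 1 − 0.5² = 0.75.

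- No clustering: 0.7/√(2 × 0.75/44) = 3.791, power 96.6%.
- k = 4, ICC 0.05, therapist variance left unreduced: variance = 0.05/4 + 0.95 × 0.75/44 + 0.75/44 = 0.0457; 0.7/√0.0457 = 3.273; power about 90.5%. If therapist variance shrinks in the same proportion, power is about 92%. Both are normal approximations.

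**The case against.** **The clustering is inferred.** No section gives the number of therapists or their caseloads, or says whether one therapist stays with a participant throughout. If therapists rotate, the simple nested formula does not apply. This stands, and the point is conditional for that reason. Some sharing is nevertheless hard to avoid with 59 people allocated to the intervention.

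**The size rests on assumption.** The largest figure, 13.1%, needs 3 therapists and ICC 0.10 together. At 6 to 9 therapists and ICC 0.01 to 0.02, type I error is 5.2% to 5.7%. This also stands: the range cannot show that the problem is material in this trial.

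**A reader might infer that 90% is a best case, or holds only if therapist effects are zero.** The documents do not support that. SAP 6.6 adjusts for baseline BGSI, which the sample size ignores, and step 5 shows this can offset moderate clustering. Protocol 7.1 also builds in a wide SD: a 2-point difference at 0.7 "would require SD of the measure to be approximately 2.86", against a baseline SD of 1.74 in the trial it cites. These points concern power only. Neither corrects an interval that omits therapist variance.

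**Therapists could be treated as fixed.** If inference is confined to the therapists used, leaving out a random effect is defensible. But the planned manual is meant for use beyond them, so the wider inference is at least worth showing.

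**Conclusion.** The point holds in conditional form. Therapy is individual and given in one arm, the sample size assumes independent outcomes, and neither the primary model nor any sensitivity analysis includes therapist. If participants share therapists and therapists differ, the primary interval is too narrow, and neither the site effect nor baseline adjustment repairs it.

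Under the assumed 3 to 9 therapists and ICC 0.01 to 0.10, the nominal 5% error is about 5.2% to 13.1%. It matters in practice only with few therapists and an ICC of 0.05 or more. The effect on power cannot be signed overall, because the missing clustering allowance and the uncredited baseline adjustment pull in opposite directions. If one therapist had treated the whole arm, therapist and treatment could not be separated by any model.

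**What to change.** - Keep the SAP 6.6 model as primary.
- Record a therapist ID for each intervention participant. The documents do not show whether this is already captured; SAP 5.1 refers to a separate Data Management Plan.
- Add to SAP 6.9 a sensitivity analysis of 3-month BGSI attainment with a therapist random effect in the intervention arm only, arm-specific residual variance and small-sample degrees of freedom. Place it in the unblinded report with the session-based analyses, so the blinded stage is unaffected.
- Report the number of therapists, their caseloads, and the ICC with its interval. If the primary and sensitivity intervals lead to different conclusions, say so and qualify the conclusion.
- In SAP 4.1, state that the 90% assumes independent outcomes and takes no credit for covariate adjustment. Any power range given should use the same small-sample degrees of freedom as the sensitivity model; the normal-approximation figures would not match it (83.6% against about 73% at 4 therapists and ICC 0.05).

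The cost is SAP wording, one identifier and one extra model. The downside is that with few therapists the ICC is imprecise and the sensitivity interval wide, which is why this is a sensitivity analysis and not a replacement for 6.6.

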#### 5.2.2.1 Trial design

This will be an individually randomised parallel group controlled trial, comparing the study intervention (cognitive rehabilitation) with the clinical standard of care (current clinical management pathways for long Covid, including treatment for fatigue, respiratory disorders, sleep, anxiety and depression).

590

591 5.2.2.2 Participant flow

592

593 Post-consent participants will undergo baseline assessment before randomisation to receive  
594 either neuropsychological rehabilitation or treatment as usual.

595

596 5.2.2.3 Outcome measures

597

598 The primary outcome will be participant-reported goal attainment at 3 months post-  
599 randomisation. This will also be collected at the 6 month post-randomisation follow up. This  
600 will be collected using the Bangor Goal Setting Interview (BGSi).

601

602 Secondary outcomes will be:

- 603 • Cognitive function (tested using the cognitive batteries employed for Workstream 1)
- 604 • Quality of life (EQ-5D-5L)
- 605 • Life Space Assessment
- 606 • Social Functioning (SF-DEM)
- 607 • Instrumental Activities of Daily Living (IADL) Scale
- 608 • Generalised Anxiety Disorder Assessment (GAD-7)
- 609 • Patient Health Questionnaire (PHQ-8)
- 610 • Chalder Fatigue Scale
- 611 • Pittsburgh Sleep Quality (PSQI)
- 612 • DePaul Symptom Questionnaire – Post-Exertional Malaise (DSQ-PEM).
- 613 • Client Service Receipt Inventory (CSRI)

614

615 5.2.2.4 Health economic analyses

616

617 From a public sector, multi-agency perspective we will conduct an economic evaluation to  
618 determine the incremental cost-effectiveness of the intervention in comparison to clinical  
619 standard of care. The intervention of interest will be a novel neuropsychological rehabilitation  
620 intervention programme for cognitive Covid compared to clinical standard of care (i.e. current  
621 clinical management pathways for long Covid, including treatment for fatigue, respiratory  
622 disorders, sleep, anxiety and depression). We will examine two research questions during  
623 the economic evaluation:

624

- 625 1. What is the incremental cost-effectiveness of CICERO-Rehab compared to standard  
626 clinical care for cognitive Covid?
- 627 2. What is the cost per QALY of CICERO-Rehab compared to standard clinical care for  
628 cognitive Covid, and does this fall below the NICE threshold of £20,000 to £30,000  
629 per QALY?

630

631 The clinical trial will provide data pertaining to cost, intervention characteristics, outcomes  
632 and other health/economic data which will be used during the health  
633 economic evaluation. Analysis with complete and well-structured data is preferable but we  
634 are often faced with the possibility of missing data and/or skew data resulting from several  
635 issues such as incomplete data and patient withdrawal. To handle these issues an  
636 appropriate Statistical Analysis Plan (SAP) such as the Bayesian simulation method,  
637 an imputation method or complete case analysis will be conducted. Our choice of method  
638 will be determined by the quantity and quality of primary data. All relevant data inputs will  
639 undergo full validation and verification by the trial team, and uncertainty will be considered  
640 within the sensitivity analysis. Discounting of costs and outcomes will not be relevant as the  
641 follow-up period is less than 12 months.

642

#### 643 Health economic outcome measures

644

645 For the primary cost-effectiveness analysis, the primary outcome will be QALYs, derived  
646 from the EQ-5D-5L outcome measure. The EQ-5D-5L is a generic, preference based,  
647 health-related quality of life (HRQoL) measure. It consists of two parts, a five  
648 item questionnaire and a visual analogue scale (EQ-VAS). The EQ-5D-5L questionnaire is  
649 scored between 0 and 1, with 1 meaning full HRQoL and 0 death (some scores may fall  
650 below 0). Each set of answers on the EQ-5D-5L is assigned a utility score between 0 and 1  
651 based on general population weighting of health states. This measure can then be used to  
652 generate QALY estimates by assigning a quality of life weight to the length of time a person  
653 is in a given health state.

654

655 Secondary cost-effectiveness analyses will be conducted using the Bangor Goal Setting  
656 Interview and HADs outcome measures. These will be used to develop incremental cost-  
657 effectiveness ratios (ICERs) to express cost-effectiveness in natural units of effect, which will  
658 in turn allow comparison with the QALY outcomes. Comparing these outcomes will help to  
659 determine relative agreement between the generic QALY outcomes and 23 clinically relevant  
660 outcomes.

661

